This paper describes the protocol of the PREVIEW (PRedicting the EVolution of SubjectIvE Cognitive Decline to Alzheimer's Disease With machine learning) study, which will prospectively investigate baseline predictors and biomarkers of Alzheimer's pathology and progression to MCI and dementia in a large cohort of patients with SCD. In this study, we will integrate our previous findings with data from non-invasive techniques, such as electroencephalography (EEG) and event-related potentials (ERP) recording. These techniques reliably measure neural circuits associated with cognitive processes and may provide sensitive metrics for early diagnosis of cognitive impairment [24]. Additionally, we will employ machine learning approaches, an emerging and promising tool that has demonstrated great potential in diagnosing and classifying neurodegenerative diseases and other medical conditions [25–27].

Specifically, our aims are as follows:i)Integrate a multimodal set of data from SCD patients, including clinical data, neuropsychological assessments, personality traits, cognitive reserve, genetic factors, and features from EEG and ERP recordings.ii)Train and test a machine learning model based on these features to predict biological AD pathology (defined according to CSF biomarkers) and conversion from SCD to MCI and AD dementia through machine learning tools.iii)Define a management protocol for SCD to be applied in memory clinic settings.

The PREVIEW study was registered on ClinicalTrials.gov (registration number: NCT05569083).

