### Machine learning classification of patient conditions

Demographic, clinical, cognitive, neurophysiological, and genetic data will be used as candidate input features without any further processing for training a machine learning model. During the training process, a feature selection algorithm will be applied to select the most informative features based on their performance on the validation set.

The machine learning problem will initially be treated as a multi-class classification task. The model will classify patients who are SCD at the time of the measurements into one of the following three classes: stable SCD, progressed to MCI, or progressed to AD dementia. For the subgroup of patients undergoing CSF biomarker analysis, a classification will be performed based on the results of the analysis. Specifically, patients will be classified as carriers or non-carriers of AD pathology, according to the NIA-AA framework [9].

For feature selection, we will test the efficacy of several algorithms including the ANOVA F-test statistic, ReliefF, mutual information, and minimum redundancy maximum relevance (MRMR). The number of retained features for each algorithm will be optimized in the validation loop.

Regarding the classifier models, a set of different machine learning models will be tested, including support vector machine (SVM) with linear, quadratic, cubic, and radial basis function kernels; random forest (RF); gradient boosted trees (xgboost); linear and quadratic discriminant analysis (LDA and QDA); and an artificial neural network (ANN). The hyperparameters of each algorithm will be optimized to determine the model with the best performance in the classification task.

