In the SVM, the parameters C (misclassification penalty) and gamma (influence of single training points) will be optimized. For the RF, the number of trees (estimators), maximum depth of each tree, and minimum number of data points allowed in a leaf node will be optimized. The same hyperparameters will be tuned for xgboost, along with the learning rate of the algorithm. In LDA and QDA, the type of solver used by the algorithm and the shrinkage term will be adjusted. For the ANN, the number of layers and neurons per layer will be optimized. We have chosen to compare feature selection methods from classical statistics (such as ANOVA F-test) with data-driven methods (ReliefF and MI) that do not assume the distribution of the data. Additionally, the MRMR algorithm will be tested to consider possible redundancies among features.

In the machine learning models, both linear (linear SVM and LDA) and non-linear (polynomial and radial basis function [RBF]-SVM and QDA) algorithms that define separating hyperplanes will be tested, along with tree-based methods like RF and xgboost. The ANN will serve as a non-linear, black-box model to assess the discrimination performance and potential overfitting of more complex models. Furthermore, standard dimensionality reduction techniques will be applied to extract the most salient features. The procedure described above will be repeated to evaluate whether similar results can be achieved with a subset of the features. Once the cross-sectional classification is performed, longitudinal data will be utilized to develop an algorithm capable of predicting the future progression of cognitive impairment.

Out of the entire dataset, 30% of the data will be reserved as a testing set, while the remaining 70% will be used for training and validation of the model. A fivefold cross-validation approach will be employed to train and optimize the hyperparameters of the models. The best performing model, determined by the prediction F1-score and the set of optimized hyperparameters, will be tested on the testing set to obtain an unbiased estimate of the model's performance.

A visual summary of the data collection and analysis process is shown in Fig. 2.

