This approach offers several advantages over classical statistics. Firstly, it allows us to consider all the collected variables simultaneously. Secondly, the machine learning procedure helps identify the most informative features for screening, enabling the development of a protocol that reduces the burden on patients and healthcare costs associated with cognitive assessments.

Furthermore, this approach will provide additional evidence to clarify the role of certain variables that still have controversial associations with SCD. For example, numerous studies have shown that individuals with SCD have lower scores on neuropsychological tests compared to those without SCD [78–80]. However, only a few longitudinal studies have assessed the prognostic value of baseline neuropsychological assessments, often yielding conflicting results [81–84].

Several studies have focused on the relationship between SCD and cognitive reserve [85–89]. Engaging in intellectual activities during earlier decades and having higher premorbid intelligence have been identified as protective factors, reducing the risk of progression from SCD to MCI [15, 16]. However, cognitive reserve seems to have a dual effect, as individuals with higher cognitive reserve exhibit faster disease progression once it begins [16, 90]. The interaction between SCD and mood disorders is also controversial. Recent community-based studies on large populations have shown that depressive symptoms increase the risk of progression to objective cognitive decline and dementia in SCD patients [91, 92]. However, a meta-analysis by Huang et al. found that depression was significantly higher in individuals with SCD compared to normal individuals, but there was no difference between SCD and MCI, or between SCD converters and non-converters [93]. Studies on personality traits have yielded conflicting results regarding their association with SCD. Most studies agree that high conscientiousness and low neuroticism are associated with a reduced risk of incident AD [94, 95]. However, a previous study found that emotional stability was significantly higher in SCD patients who progressed to MCI or AD dementia [96].

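### Reduction by feature is not set up to show which whole assessments, notably resting EEG and ERP, could be left out of a less burdensome protocol

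*Protocol article*

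**What the plan says.** All places are in the protocol article.

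- **The promise.** The Discussion lists identification of the most informative features as an advantage of machine learning, "enabling the development of a protocol that reduces the burden on patients and healthcare costs associated with cognitive assessments". Aim iii in the Background reads "Define a management protocol for SCD to be applied in memory clinic settings".
- **Unit of selection.** Under *Machine learning classification of patient conditions*, "a feature selection algorithm will be applied to select the most informative features based on their performance on the validation set". The filters to be tested are the ANOVA F-test, ReliefF, mutual information and MRMR.
- **How many are kept.** "The number of retained features for each algorithm will be optimized in the validation loop". No burden or cost term is stated.
- **Further reduction.** In the same section, "standard dimensionality reduction techniques will be applied to extract the most salient features"; no technique is named. The procedure is then repeated to "evaluate whether similar results can be achieved with a subset of the features".
- **What patients undergo.** A neuropsychological battery (Table 1), a personality questionnaire, a leisure-activity interview, blood sampling with APOE and BDNF genotyping, resting EEG and an ERP task battery. Lumbar puncture is optional and supplies the biological outcome.

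No comparison of models with and without a given assessment is stated.

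**The concern.** Much of the burden and cost arises when a test, questionnaire or recording session is carried out. The Discussion moves from a list of informative features to a lighter protocol. That step is sound where one feature corresponds to one test. It is not sound where a single session yields many features, because the session must be run in full to obtain any one of them.

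A short list of selected features could therefore still call for a 64-channel resting EEG and an ERP session. The study would have no estimate of what is lost by leaving either out, and that is what a memory clinic would want to know before adopting or skipping them.

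**Working it through.** **1. The plan's own figures, needed only for the size of the test set.** Inputs from *Sample size calculation*: alpha 0.05, power 0.80, d = 0.6. A two-sided two-sample t-test (sidedness is not stated) gives 44.59, so 45 per group, as the article says. Total 2 x 45 = 90; with dropout 90 x 1.10 = 99, also as stated. The 30% test share is 0.30 x 90 = 27 to 0.30 x 99 = 29.7, about 30 patients.

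**2. Features per assessment.** From *EEG Statistical analysis*: 6 regions x 4 bands = 24 relative-power features from one resting recording, before connectivity, network and microstate metrics. At the other end, a test such as the MMSE or MAC-Q is taken here to give one score.

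**3. Chance that an assessment drops out entirely.** The article gives neither the total number of features p nor the number kept k. Illustration with p = 80-120 and k kept at random:

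P(none of m features kept) = C(p - m, k) / C(p, k)

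| k kept | m = 24 (EEG power) | m = 1 (single score) |
|---|---|---|
| 5 | 0.16-0.32 | 0.94-0.96 |
| 10 | 0.02-0.10 | 0.88-0.92 |
| 20 | below 0.01 | 0.75-0.83 |

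Feature selection thus tends to remove single-score tests and keep multi-feature sessions, for reasons of count alone. Random selection is not the plan; it only isolates this effect.

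**4. How many of six assessments remain.** All set-ups are assumed. Those with equal blocks have 6 x 20 = 120 features and keep 10. The simulations use 63 training patients (70% of 90), d = 0.6 per predictive feature and within-assessment correlation of about 0.4.

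| Set-up | Assessments still needed, of 6 |
|---|---|
| Equal blocks, random 10: 6 x (1 - C(100,10)/C(120,10)) | 5.1 |
| Uneven blocks 25/5/23/2/60/120, random 10 | 3.6 |
| Uneven blocks, random 20 | 4.3 |
| Two predictors in every assessment | F-test 5.2, MRMR 5.8 |
| Signal in two assessments only, 10-20 predictors each | F-test 2.2-2.8, MRMR 4.3-4.7 |
| Signal in two assessments only, 2 predictors each | F-test 4.4, MRMR 5.5 |

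The count runs from about 2 to nearly 6, so no single figure can be given for this study. In the simulations MRMR keeps more assessments than the F-test. It penalises overlap between features, which spreads the choice across assessments when features correlate more within than between them.

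**5. Dimensionality reduction.** In a simulated 63 x 84 data set, each of the first five principal components had non-zero loadings on all 84 inputs. A PCA-type reduction therefore removes no measurement. The article does not name PCA, so this step is conditional.

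**6. Precision of a full-versus-reduced comparison on the test set.** For paired predictions with no true difference, the 95% half-width for the difference in accuracy is 1.96 x sqrt(discordance / n).

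- 10% discordant (assumed): 0.119 with n = 27, 0.113 with n = 30.
- 30% discordant (assumed): 0.207 with n = 27, 0.196 with n = 30.

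That is roughly 11-21 percentage points. The plan ranks models by F1-score; accuracy is used here because the formula is simple.

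**The case against.** The strongest reply has five parts.

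- **The promise concerns cognitive assessments, and feature selection can shorten those.** Table 1 has 22 rows, many giving one or a few scores. This stands: for such tests, dropping the feature largely drops the test. A reader might infer that the plan cannot show that any assessment is dispensable; the article does not support that.
- **Aim iii does not promise a shorter protocol.** This also stands. It asks for a management protocol, and much of the article's cost argument compares its measures with PET and CSF. It would be wrong to say that aim iii cannot be answered. The mismatch is with the Discussion sentence on burden and cost.
- **A figure such as 5 of 6 assessments remaining is built in by the set-up.** Correct. It comes from equal block sizes or from placing signal in every block, and other set-ups give much lower counts.
- **The dimensionality reduction is unnamed and may mean selection.** Correct. The projection point is conditional, and the feature-level point does not need it.
- **A re-run on fewer features is planned, and its detail belongs in an analysis plan not shown here.** This stands in part. The re-run is the natural place for the comparison, and an unseen document may define its subsets by assessment. But the article describes its reduction steps throughout by feature and then draws a conclusion about burden from them. That is a mismatch within the text shown, not just missing detail.

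**Conclusion.** The point holds in a limited form. Selection and the reduced re-run are organised by feature, while the expected gain in burden and cost depends partly on which assessments are carried out. For single-score tests the two coincide. For resting EEG, with at least 24 features, and for ERP, which supplies spectral and voltage features, they do not: one retained feature keeps the session. If projection is used, all inputs stay.

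Followed as written, the plan would give a feature list that need not show which sessions can be omitted. The number that would remain is not determined by the article; it rests on assumed feature counts and on where the signal lies. The prediction aims themselves are unaffected, and no stated figure changes.

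**What to change.** Define the planned re-run by assessment. One possible set of blocks is: demographics and brief tests; full neuropsychology; questionnaires; genotype; resting EEG; ERP. Run the same pipeline, including feature selection and tuning, with each block added in turn or left out. Report the change in performance with an interval for each block, preferably from cross-validation or resampling as well as from the test set. If one reduced set is put forward, choose it within the 70% training share, so that the test set still gives an unbiased estimate.

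Do not offer projection components as evidence for a reduced protocol; keep them, if wanted, as exploration.

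**Cost.** Extra model runs on data already collected, with no change for patients or visits. Six cumulative sets plus six leave-one-out sets, less one that coincides (all but ERP), make 11 sets including the full model, so at most 10 extra runs. The intervals will be wide, as shown above. The results should be reported as estimates of what each block adds, not as proof that a block is dispensable.

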### Sample size calculation

We estimated the sample size needed for this study using the statistical power of a hypothesis test using the Python module statsmodels [32]. We considered the following parameters:Level of significance (α) = 0.05Statistical power (1-β) = 0.8Effect size (Cohen's d) = 0.6

The required number of patients was 45 per group. Therefore, considering that we aim to compare patients who will show a progression to objective cognitive decline and patients who will not, the total estimated sample size should be 90 individuals.

With an expected conservative drop-out rate of 10%, the number of participants to be included was estimated to be 99 patients.

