### Descriptive statistical analysis

Descriptive statistical analyses will be conducted using IBM SPSS Statistics Software Version 25 (SPSS Inc., Chicago, USA) and the computing environment R4.2.3 (R Foundation for Statistical Computing, Vienna, 2013). The distributions of variables will be assessed using the Shapiro–Wilk test. Patient groups will be characterized using means and standard deviations, medians and interquartile ranges (IQR), frequencies or percentages, and 95% confidence intervals (95% C.I.) for variables with continuous distribution, continuous non-normally distributed variables, and categorical variables, respectively. Depending on the distribution of the data, we will employ ANOVA or non-parametric Kruskal–Wallis tests for between-group comparisons, and Pearson's or Spearman's correlation coefficient to assess correlations between numeric measures of the groups. Chi-square tests will be used to compare categorical data. Effect sizes will be computed using Cohen's *d* for normally distributed numeric measures, η^2^ for the Mann–Whitney-U Test, and Cramer's *V* for categorical data.

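### Whether a feature subset gives similar results is to be judged by rerunning the model search, which yields a second point estimate that cannot support a claim of similarity at this sample size

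*Protocol article*

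**What the plan says.** The section on machine learning classification sets out four feature-selection methods, several classifier families, the hyperparameters to be tuned, fivefold cross-validation and a hold-out: "30% of the data will be reserved as a testing set, while the remaining 70% will be used for training and validation of the model". The metric for choosing a model is F1: "The best performing model, determined by the prediction F1-score and the set of optimized hyperparameters, will be tested on the testing set".

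After a sentence on dimensionality reduction, the same section adds: "The procedure described above will be repeated to evaluate whether similar results can be achieved with a subset of the features". That is all the article says on how similarity will be assessed. It does not define similar, and it gives no difference between models, no interval for such a difference and no tolerable loss. Confidence intervals appear only in the section on descriptive analysis, where they describe patients: "Patient groups will be characterized using means and standard deviations, medians and interquartile ranges (IQR), frequencies or percentages, and 95% confidence intervals".

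Feature reduction has a stated purpose. The Discussion says that identifying informative features helps in "enabling the development of a protocol that reduces the burden on patients and healthcare costs associated with cognitive assessments", and the third aim in the Background is: "Define a management protocol for SCD to be applied in memory clinic settings".

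**The concern.** Asking whether a subset does about as well as the original feature set is a non-inferiority question. The answer depends on the largest loss the data can exclude, not on whether two estimates happen to lie close together. Rerunning the search produces the second estimate and stops there. In a small test set two models can score alike by chance when one is truly worse, and equally good models can score apart.

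At stake is whether an assessment with real predictive information is judged dispensable on evidence that cannot exclude a material loss. The article presents lower patient burden and cost as benefits of the approach, so a statement that a subset performs similarly is likely to be used.

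**Working it through.** **1. The plan's own sample size.** With d = 0.6, two-sided alpha 0.05 and power 0.80, the normal approximation gives 2 × (1.96 + 0.84)² / 0.6² = 43.6, so 44 per group. The t-test solution in statsmodels is 44.59, so 45. This matches the article: "The required number of patients was 45 per group". Then 2 × 45 = 90, and 90 × 1.10 = 99. The figure reproduces, but it concerns a difference between progressors and non-progressors. No figure in the article concerns the comparison of two models.

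**2. Test-set size.** 0.30 × 90 = 27; 0.30 × 99 = 29.7, so 30.

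**3. Assumptions (not in the documents).** Accuracy stands in for F1, and each prediction is right or wrong. True accuracy is 0.80 for the original model and 0.70 for the reduced model. Correctness of the two models on the same patient follows a bivariate normal latent variable with correlation 0.5 or 0.8. This gives:

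| Latent correlation | Only original correct | Only reduced correct | Discordance q |
|---|---|---|---|
| 0.5 | 0.185 | 0.085 | 0.270 |
| 0.8 | 0.140 | 0.040 | 0.180 |

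**4. Precision of the paired difference.** Half-width = 1.96 × √((q − d²)/m), with d = 0.10, so d² = 0.01.
- m = 27: 1.96 × √(0.260/27) = 0.192; 1.96 × √(0.170/27) = 0.156.
- m = 30: 1.96 × √(0.260/30) = 0.182; 1.96 × √(0.170/30) = 0.148.

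Simulated intervals give much the same range, about 0.14 to 0.19.

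**5. How often a 10-point loss looks small.** An observed loss of 5 points or less means that the reduced model gets at most one net patient more wrong (1/27 = 0.037; 1/30 = 0.033; two patients would exceed 0.05). Simulating the discordant counts gives:

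| Test patients | Correlation | Observed loss ≤ 5 points | Equal or better |
|---|---|---|---|
| 27 | 0.5 | 33% | 20% |
| 27 | 0.8 | 29% | 15% |
| 30 | 0.5 | 30% | 18% |
| 30 | 0.8 | 25% | 13% |

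Setting the discordance directly at 0.2 to 0.3 gives 27 to 33% and 14 to 21%. A separate simulation on F1 with 27 patients and two outcome classes gives 25 to 31% and 12 to 19%.

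**6. Larger losses.** At discordance 0.3, a true 15-point loss appears as 5 points or less in about 15 to 17% of studies, and a true 20-point loss in only 5 to 7%.

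**7. What margin could be met.** If both models truly have accuracy 0.80, then q is 0.142 (correlation 0.8) or 0.226 (correlation 0.5). The margin excluded with 80% power at one-sided 0.025 is (1.96 + 0.84) × √(q/m).
- Test set: 2.80 × √(0.142/30) = 0.19 to 2.80 × √(0.226/27) = 0.26.
- All 90 patients: 2.80 × √(0.142/90) = 0.11 to 2.80 × √(0.226/90) = 0.14.

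The half-width with all 90 is 1.96 × √(q/90) = 0.078 to 0.098. A margin of that size would be met only about half the time under true equality, so it should not be taken as the achievable margin.

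**The case against.** The strongest reply is that this is an article, that the rerun is a secondary step, and that a margin and interval method are details usually left to a full analysis plan. That limits the weight of the point but does not remove it. The article goes down to kernels and tuning parameters and does state how similarity will be evaluated. A small margin added later could not reliably be met with 27 to 30 test patients.

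Several stronger readings are tempting, and the documents do not support them:
- *That similarity will be declared from a non-significant test.* No test between classifiers is named. The tests in the descriptive section compare patient groups.
- *That the plan would pass a markedly inferior battery as similar.* It states no threshold. The 5-point yardstick is this review's, and a true 20-point loss would seldom look that small.
- *That the clinic protocol of the third aim rests on this rerun.* The Discussion credits the machine learning procedure generally with finding informative features, and the aim mentions no reduced set. The link is an inference.
- *That the contrast is between all features and a subset on one shared test set.* The main procedure already selects features, so this is probably a contrast of two selected models. The sentence comes before the hold-out paragraph, which sends one best model to testing. If the comparison is made within the 63 to 69 training patients, the test-set figures do not apply. The formula in step 4 then gives half-widths of 1.96 × √(0.170/69) = 0.10 to 1.96 × √(0.260/63) = 0.13, still wide, and the same scores will have been used to choose the models.

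It also stands that the plan's initial outcome has three classes, whereas the calculation treats predictions as right or wrong.

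**Conclusion.** The concern holds as a limited point about a secondary analysis. The article poses a similarity question and gives as its analysis a rerun that returns only a second point estimate. If the comparison is made on the 30% test set, a true 10-point loss would look like 5 points or less in about 25 to 33% of studies, and the paired difference would carry a 95% half-width of about 0.14 to 0.19. These sizes rest on assumed accuracies of 0.80 and 0.70, assumed correlation between the models' errors, and accuracy in place of F1. The need for an interval and a pre-set loss does not depend on those values. The point does not invalidate the study or its main classification.

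**What to change.** Replace the sentence on the feature subset with a rule along these lines: the original and reduced-feature models will be scored on the same patients; the paired difference in the chosen metric (reduced minus original) will be reported with a bootstrap 95% confidence interval; the reduced set will be called similar only if the lower bound lies above a tolerable loss that the investigators fix before the comparison; otherwise the comparison will be reported descriptively, with a statement that similarity was not shown.

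The 70/30 split need not change. Both models have to be applied to the test patients, and the article should say so. Pooled out-of-fold predictions over all patients may be added as a supporting analysis, at some extra computing cost because those predictions would have to be generated.

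The cost is a few sentences and a paired bootstrap, with no new patients or procedures. The downside is that similarity will probably not be demonstrable for small margins. The report should say this, and should cite the margin of about 0.11 to 0.14 needed even with all 90 patients rather than the narrower half-width.

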The final statistical analysis will involve extracting microstate maps [61] for each subject individually. Initially, a set of common microstates will be extracted from all subjects, regardless of conditions, using the modified k-means algorithm [62]. Then, individual microstate maps will be generated, and the template maps will be matched with the previously obtained grand-averages. The EEG signals of each subject will be reconstructed as a sequence of microstates by assigning each topography to the most similar microstate average map. From the reconstructed microstate sequence, various metrics such as duration, transition probability, and complexity of the sequence will be used as features. Spectral features, network metrics, and microstate features will be compared across conditions, providing the foundation for the machine learning analysis.

Regarding the ERP data, both spectral features (like the EEG processing) and voltage-level signals (amplitude, latency, integral of the signal) from different phases of the ERP will be used as input features.

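### One 30% hold-out leaves only about 27 to 30 test patients, too few for a precise performance estimate, and all-subject EEG steps leave its unbiasedness not fully assured

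*Protocol article*

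**What the plan says.** The Sample size calculation section states that "The required number of patients was 45 per group" and that "the total estimated sample size should be 90 individuals". Allowing 10% for drop-out, it plans to include 99.

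The section Machine learning classification of patient conditions defines a three-class outcome (still SCD, moved on to MCI, moved on to AD dementia). It adds a second classification by CSF biomarkers, for the patients who have them. It states that "30% of the data will be reserved as a testing set", with the other 70% used for training and validation under fivefold cross-validation. The best model by F1-score "will be tested on the testing set to obtain an unbiased estimate" of performance. Feature selection is scored on the validation set, and the number of features is tuned in the validation loop. The section also says: "The procedure described above will be repeated to evaluate whether similar results can be achieved with a subset of the features".

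In the EEG Statistical analysis section, "a set of common microstates will be extracted from all subjects, regardless of conditions". Spectral, network and microstate features "will be compared across conditions, providing the foundation for the machine learning analysis".

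**The concern.** The study's main product is an estimate of how well SCD progression, or AD pathology, can be predicted. That estimate comes from one random split of a small cohort. If the test set is very small, one result is compatible with both poor and excellent discrimination, and another split could give a different message. Aim iii is a management protocol for memory clinics, which such a result could not support.

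A hold-out estimate is unbiased only if nothing learned from the test patients shapes the model. Two EEG steps are described on all subjects, or without a stated limit to training patients, so it has to be asked whether the claimed property is secured.

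**Working it through.** **1. Planned size.** Inputs from Sample size calculation: α = 0.05, power 0.80, d = 0.6. A two-sided two-sample t-test needs 44.59, so 45 per group and 90 in total; the plan's figure is reproduced. For drop-out, 90 × 1.10 = 99 (90/0.90 would give 100).

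**2. Size of the test set.**
- 0.30 × 90 = 27; 0.30 × 99 = 29.7, about 30. Training and validation keep 63 to 69.
- Progressors (MCI and AD dementia together) under the plan's 45:45 case: 0.5 × 27 = 13.5 to 0.5 × 30 = 15.
- Progressors if 30% progress: 0.3 × 27 = 8.1 to 0.3 × 30 = 9. If 10% progress: about 3. The article gives no progression rate, so both are assumptions.
- CSF classifier: uptake of lumbar puncture is not given. At an assumed 30% to 70%, 0.3 × 90 × 0.3 = 8.1 to 0.3 × 99 × 0.7 = 20.8 test patients.

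The AD dementia class may be smaller still: the Discussion itself cites about ten years on average to dementia.

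**3. Precision (exact Clopper-Pearson 95% intervals).** The plan ranks models by F1. Accuracy and sensitivity are used here because they have exact intervals; the observed values are illustrative.

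| Measure | Observed | 95% interval |
|---|---|---|
| Accuracy | 21/27 (78%) | 58% to 91% |
| Accuracy | 24/30 (80%) | 61% to 92% |
| Sensitivity, 45:45 case | 12/15 (80%) | 52% to 96% |
| Sensitivity, 30% progress | 7/9 (78%) | 40% to 97% |

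A half-width of 10 points at 80% would need 1.96² × 0.8 × 0.2 / 0.1² = 61.5, so 62 test patients.

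**4. What using all patients would give.** Out-of-fold predictions on all 90, with 72/90 (80%) correct, give about 70% to 88%. This is a binomial approximation, because out-of-fold predictions are not fully independent. A simulation with an assumed modest signal gave an SD of the AUC estimate of about 0.11 for one 70/30 split, against 0.07 to 0.08 for repeated fivefold cross-validation on all patients.

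**5. Separation of the test patients.** Each step as described:
- Feature selection and tuning: in the validation loop, outside the test set.
- Microstate templates: from all subjects, so later test patients help to define the features. No outcome label enters.
- Comparison across conditions: uses group labels; no limit to training patients is stated, and no use for choosing features is stated either.

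**6. Conditional worst case.** Suppose that comparison did choose features, and that its groups were the outcome classes. Simulated with pure noise, N = 90, 30% hold-out, the 10 best of p features kept (p assumed), and 50% or 30% progressors:

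| p | Mean test AUC, screened on all patients | Mean test AUC, screened on training only |
|---|---|---|
| 50 | 0.72 to 0.74 | 0.49 to 0.50 |
| 100 | 0.78 to 0.79 | 0.49 to 0.50 |
| 200 | 0.82 to 0.84 | 0.51 |

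The true value is 0.50 throughout. The effect of the label-free template step was not simulated.

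**The case against.** A hold-out with inner fivefold tuning is an accepted design, and the article does reserve the test set. Feature selection and its tuning sit in the validation loop, and the Fig. 2 legend places selection inside the cross-validated framework. The article promises an unbiased estimate, not a precise one. Intervals and details of the split may be left to a fuller plan. Nested cross-validation cannot create more progressors.

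Most of this stands, and it rules out three stronger readings that a reader might infer:
- **That the test set is contaminated and the estimate therefore biased.** Small size causes imprecision, not bias. The templates are label-free. The comparison across conditions is not said to select features, and its conditions could be the baseline groups (SCD, healthy controls, MCI patients) rather than the progression classes.
- **That an inflation to an AUC near 0.8 is to be expected.** That figure needs label-based screening on all patients, which the article does not describe.
- **That the reduced-feature rerun re-uses the test patients.** The sentence on repeating the procedure comes before the split is introduced, and only the single best model is said to be scored on the test set.

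What does not stand is the defence of the size. The single 30% split is stated, not omitted, and at this sample size it discards precision that the same patients could supply.

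**Conclusion.** The precision point holds in full. The headline performance would rest on about 27 to 30 patients over three classes, with exact intervals of 58% to 91% for an accuracy of 21/27 and 52% to 96% for a sensitivity of 12/15. The latter uses the plan's own equal split, so the conclusion does not depend on an assumed progression rate; a lower rate, or the CSF subgroup, makes it worse.

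The point on bias holds only as a gap in assurance. Templates built on all subjects break strict separation, probably with small effect. The comparison across conditions is an open risk: material (noise AUC about 0.7 to 0.84 instead of 0.5, under the assumed feature counts) only if it guides feature choice on the outcome classes. The article does not establish that it does.

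**What to change.** Replace the single 70/30 split by repeated stratified nested cross-validation on all patients. Do feature selection, tuning and classifier choice in the inner loop. Take performance, with an interval, from the outer loop. Fit the microstate templates, and any group comparison that informs feature choice, within training folds only. Run the reduced-feature models through the same outer loop. Refit the final model on all data.

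Cost: more computing time and re-coding of the microstate step. There would no longer be one untouched test set, and the outer loop evaluates the modelling procedure rather than the one refitted model. No extra patients, visits or measurements are needed.
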